### Statistical analysis of data

The comparison of the clinical and demographic characteristics of the participants between the two groups will be performed using the Pearson chi-square test for categorical variables. The Mann–Whitney test will be used to compare the severity of OM and concentration of cytokines between the two groups. The Friedman test will be used to compare changes in outcomes in the different time points for each of the treatment groups. In case of nonrejection of the null hypothesis, a post-hoc power analysis will be performed to test whether the study has sufficient power to identify the differences between groups. Values of *p* < 0.05 will be considered statistically significant. The statistical analysis will be performed using the IBM SPSS 20.0 statistical package (SPSS Inc., Chicago, IL, USA).

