Antunes et al. [29] conducted a cost-effectiveness study regarding the use of PBMT in the treatment of OM, taking into consideration the public health system perspective and the prevention of severe OM as the effectiveness measure. The authors concluded that the patients treated with PBMT presented an incremental cost of US$1689.00, when compared with the patients not exposed to PBMT; the incremental cost-effectiveness ratio was US$4961.37 per severe case of OM prevented. To our knowledge, there has not been a study that has evaluated the cost-effectiveness of PBMT for the control and treatment of OM based on patient-reported outcomes. This type of study may allow a comparison between the different technologies and drugs used for the treatment of OM.

Thus, the aim of this study is to assess the cost-effectiveness and molecular effects of PBMT in the treatment and prevention of severe OM. The hypothesis is that PBMT is more costly but more effective than conventional treatment of OM and that PBMT modulates the inflammatory and oxidative stress proteins. This study will contribute to a better understanding of the PBMT mechanism and may allow the laser technology to be consolidated and used in public health systems, providing a better QoL for patients undergoing HNC treatment.

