### Participants

The participants will be HNC patients of the Brazilian public health system—Brazilian Unified Health System (Sistema Único de Saúde (SUS))—who will be treated with RT, with or without CT, in Araujo Jorge Hospital, Goiânia, Goiás, Brazil. To estimate the study sample size, we used the OpenEpi online calculator (http://www.openepi.com). The 95% significance level (1 – α error type I), a study power of 80% (1 – β error type II) and a 1.0 ratio of unexposed/exposed were set as estimator parameters. Finally, we considered a prevalence of severe OM of 60% for the control group and 21% for the PBMT group (OR = 0.18) [18]. The calculated minimum sample size was 50 participants (25 per group) and an additional 10% was considered to compensate for possible loss to follow-up.

Individuals older than 18 years of age of both sexes will be included in the study, edentulous or not, with neoplastic lesions in the head and neck site (oral cavity, oropharynx, nasopharynx and advanced stage laryngeal tumors; T3 N1 or T3 N2 and T4 with any N status). All participants will be subjected to RT (with or without CT), with a minimum dose of 50 Gy, 2 Gy/day and five times per week, in the conventional scheme of RT. All patients will be treated with the Elekta Compact (Elekta AB, Stockholm, Sweden), a linear accelerator that generates photon radiation with fixed energy of 6 MV. Participants will be excluded if they present with an infection or salivary gland tumors, Sjögren’s syndrome, are submitted to palliative treatment or were previously treated with RT and/or CT in the head and neck area. Individuals diagnosed with lymphoma, melanoma or skin cancer will also be excluded.

In this hospital setting, every HNC patient who will be submitted to RT must be evaluated by the Dental Care Service to obtain authorization before starting the HNC treatment. On this occasion, the individuals will be invited to participate in the study. After acceptance, the principle researcher will obtain a signed written informed consent form from the participants. Participants will be excluded from the trial in cases of death, withdrawal or absence from five or more laser therapy sessions.

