#### Saliva collection and analysis

The collection of saliva will be performed before initiating the HNC treatment and after the 7th, 14th, 21st and 30th RT sessions, based on the method of Oton-Leite et al. [28] and Navazesh [39]. The participants will be instructed not to eat or drink 1 h before the collection of saliva.

The collection of unstimulated saliva will be performed in an artificial light environment, with the participants sitting with their eyes open, with their head slightly tilted down, without talking, opening their mouth or swallowing the saliva during the time of collection. Initially, the participants will be instructed to wash their mouth with water and swallow any saliva in their mouth. The participants will then be instructed not to swallow for a period of 5 min in order to accumulate saliva. This accumulated saliva will be deposited in a sterile Falcon-type millimeter tube.

The sample will be centrifuged for 15 min at 4500 rpm. The samples will then be transferred to another tube and diluted (1:1) in PBS solution (0.4 mM NaCl and 10 mM NaPO_4_) containing protease inhibitors (0.1 mM phenylmethylsulfonyl fluoride, 0.1 mM benzethonium chloride, 10 mM EDTA and 0.01 mg/ml aprotinin A) and 0.05% Tween-20. The solution will be homogenized, distributed in aliquots of approximately 2 ml and frozen at − 80 °C. The concentrations of inflammatory cytokines, nitrite and total proteins will be assessed in each saliva sample.

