#### Inflammatory study

##### Cytokine study

The concentrations of the cytokines (IL-1β, IL-10, IL-6, IL-8, IL-12, TNF-α) in the saliva samples will be determined by cytometric bead array (CBA). The CBA method enables the detection of multiple soluble mediators from a relatively small sample, using bead-based flow cytometric immunoassays, since beads of different sizes or colors are used. Thus, this assay measures the levels of the six cytokines in a small sample of saliva [40].

The cytokines will be measured by a BD FACSCanto II flow cytometer (BD Biosciences, San Jose, CA, USA) using the CBA human inflammatory cytokines kit (BD Biosciences) following the manufacturer’s recommendations. Briefly, the Human Chemokine Standards will be reconstituted and serially diluted in the Assay Diluent. After this, the Human Chemokine Capture Beads will be mixed and a 10-μl aliquot of each Capture Bead, for each assay tube to be analyzed, will be placed into a single tube. A 96-well plate will be used to perform the assay. The initial wells will be filled with 50 μl of the Human Chemokine Standard; then, 50 μl of the saliva sample will be placed, followed by the addition of 50 μl of the Human Chemokine PE detection reagent. The saliva and detection reagents will be incubated for 3 h, protected from light. After this, 100 μl of wash buffer will be added to each well and centrifuged at 1100 rpm for 5 min. The supernatant will be carefully aspirated and discarded. Finally, the bead pellet will be resuspended with the addition of 150 μl of wash buffer. The values will be determined based on the negative control and a standard curve.

The Bradford method will be used to measure the total protein concentration in the saliva samples, expressed as milligrams per milliliter. This concentration will be used to adjust the salivary cytokine values for each sample. The values of the cytokine levels in saliva samples corrected for total proteins will be expressed as picograms per milligrams of protein.

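### The between-arm cytokine comparison ignores each participant's pre-treatment sample: a valid test, but less precise than one that could be run at almost no cost

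*Protocol article*

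**What the plan says.** Under Saliva collection and analysis, the Protocol article sets five samples per participant: "The collection of saliva will be performed before initiating the HNC treatment and after the 7th, 14th, 21st and 30th RT sessions". Under Cytokine study, six cytokines are measured and each value is corrected for total protein: "This concentration will be used to adjust the salivary cytokine values for each sample". The analysed quantity is therefore picograms per milligram of protein.

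Statistical analysis of data names two tests that touch these values. Between arms: "The Mann–Whitney test will be used to compare the severity of OM and concentration of cytokines between the two groups". Over time: "The Friedman test will be used to compare changes in outcomes in the different time points for each of the treatment groups". The section mentions no covariate and no change score for the cytokine comparison between arms. The planned check of baseline comparability covers only clinical and demographic features, by chi-square.

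The Background hypothesis includes the claim that "PBMT modulates the inflammatory and oxidative stress proteins". Randomisation is simple and 1:1, with 25 participants per group before the allowance for loss.

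**The concern.** The participant is randomised, and each participant supplies a pre-treatment value and four later ones. The plan splits this information. The test that uses the repeated samples makes no comparison between arms, and the test that compares arms does not use the pre-treatment sample.

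Two things follow. First, stable differences between people stay in the error term of the randomised comparison, which costs power if baseline predicts later values. Second, simple randomisation of about 50 people leaves chance differences in baseline cytokine levels. Part of any such difference passes into the on-treatment contrast and can mimic or hide an effect. As the article is written, nobody would adjust for that difference or look at it.

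At stake is the molecular half of the trial's hypothesis. With Friedman results reported arm by arm, readers may also take a significant change in one arm but not the other as evidence of a treatment effect, which it is not.

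**Working it through.** **Inputs from the article.** 25 per arm (Participants); one pre-treatment and four on-treatment samples (Saliva collection and analysis); significance at 0.05 (Statistical analysis of data), taken as two-sided.

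**Assumptions.** The article gives no SD, effect or power for cytokines and no baseline to on-treatment correlation (rho). I assume normal values on a log scale, equal SD in both arms, and rho between 0 and 0.7.

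**1. The plan's own figure.** For severe mucositis at 60% against 21% with 80% power, the pooled formula gives n = (1.96 + 0.842)² × 2 × 0.405 × 0.595 / 0.39² = 24.9 per arm. The stated 25 per group reproduces. It was not set for cytokines.

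**2. Analytic power at 25 per arm.** The SE of an unadjusted difference is √(2/25) = 0.283 SD. An unadjusted normal test has 80% power at (1.96 + 0.842) × 0.283 = 0.79 SD. Mann–Whitney, with efficiency 3/π, has 78.2% there. ANCOVA multiplies the SE by √(1 − rho²), so power = Φ(0.792 / (0.283 × √(1 − rho²)) − 1.96):

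| rho | ANCOVA | gain over Mann–Whitney (points) | plain change score |
|---|---|---|---|
| 0 | 80.0% | 1.8 | 50.8% |
| 0.3 | 83.6% | 5.4 | 65.8% |
| 0.5 | 89.9% | 11.7 | 80.0% |
| 0.7 | 97.5% | 19.4 | 95.1% |

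The 1.8 points at rho 0 are the normal test's advantage over ranks, not a gain from baseline. The change score has SD √(2(1 − rho)). It is worse than no adjustment below rho 0.5 and never better than ANCOVA here.

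**3. Like-for-like simulation.** Rank against rank, at one on-treatment visit, 4,000 runs per cell, comparing Mann–Whitney with Quade rank ANCOVA:

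| effect | rho | Mann–Whitney | rank ANCOVA | gain (points) |
|---|---|---|---|---|
| 0.60 SD | 0.3 | 52.7% | 56.1% | 3.4 |
| 0.60 SD | 0.5 | 52.0% | 62.6% | 10.6 |
| 0.60 SD | 0.7 | 51.8% | 76.9% | 25.1 |
| 0.83 SD | 0.3 | 78.6% | 82.3% | 3.7 |
| 0.83 SD | 0.5 | 78.0% | 87.3% | 9.3 |
| 0.83 SD | 0.7 | 78.3% | 96.4% | 18.1 |

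Repeat runs moved single gains by up to about two points and showed essentially no gain at rho 0. With no true effect, rejection rates were 4.3–5.2% for Mann–Whitney and 5.1–5.4% for rank ANCOVA.

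**4. Chance imbalance.** The baseline difference between arms also has SE 0.283 SD, so it exceeds 0.4 SD in either direction in about 16% of trials (0.4 / 0.283 = 1.41). The part passed on is rho times the imbalance: at rho 0.5, a one-SE imbalance shifts the contrast by 0.14 SD and a 0.4 SD imbalance by 0.20 SD.

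In a normal approximation, an unadjusted test rejects beyond 1.96 × 0.283 = 0.554 SD. Given the imbalance, the contrast has SD 0.283 × √0.75 = 0.245. With no true effect and rho 0.5, the rejection rate is 2.4% when baselines match exactly and 7.5% at an imbalance of 0.4 SD. Over all randomisations this averages to 5%.

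**The case against.** **The test is valid.** The arms hold different people, so an unpaired test is legitimate, and its error rate already allows for chance imbalance. This stands. A reader might infer that the planned test gives false positives too often. It does not: the overall rate is about 5%, and the remaining issue is precision, plus bias conditional on the imbalance that occurs.

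**No single power loss can be claimed.** This also stands. A reader might take a loss of about 10 points as a property of the trial, but that figure belongs to rho near 0.5 and a moderate effect. The Background says that radiotherapy and chemotherapy themselves drive mediator production, so pre-treatment levels may predict later ones poorly. In that case the gain is small.

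**The values are not raw.** A reader might infer from the word concentration that unprocessed values are compared. The Cytokine study section corrects them for total protein. That normalises each sample but does not use the participant's own starting level.

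**The detail may sit in an analysis plan not shown.** The article does not name the visit compared, and its quality-of-life cost-effectiveness ratio does use last minus baseline. This carries limited weight: the point concerns a test the article names, and an analysis plan that followed the article would run that test unadjusted.

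**Cytokines are secondary.** They did not size the trial and no cost-effectiveness result depends on them. The molecular hypothesis also draws on nitrite. This sets the importance but does not remove the point.

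**Conclusion.** The point holds as a matter of efficiency. The only between-arm cytokine test named leaves out a pre-treatment value that the trial collects from every participant, and the within-arm Friedman tests do not fill the gap.

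Under the stated assumptions, rank ANCOVA gains about 3 points of power at rho 0.3, about 10 at rho 0.5, and 17 to 26 at rho 0.7. It gains nothing near rho 0. Adjustment also removes the share of chance baseline imbalance that would otherwise enter the contrast.

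The documents do not support calling the planned test invalid, or fixing one figure for the loss. This is a worthwhile, nearly free improvement for an outcome that did not size the trial.

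**What to change.** In Statistical analysis of data, keep Mann–Whitney for mucositis severity, where baseline grades should be near 0 and adjustment would gain little. For cytokines, replace it with wording such as: *Each cytokine (log pg/mg protein) will be compared between groups by ANCOVA with the participant's log pre-treatment value as covariate, at [named visit]; the adjusted group difference will be reported with a 95% confidence interval.* A mixed model over the four on-treatment visits, with the same covariate, is an equally good choice. Whichever is used, the visit or contrast should be fixed before the cytokine data are analysed by arm.

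If many values fall below detection, use Quade rank ANCOVA: regress ranked on-treatment values on ranked baseline values and compare the residuals between arms. It gives a p-value but no confidence interval on an interpretable scale. Do not substitute a plain change score, for the reason shown in the working. Label the Friedman tests as description within arms.

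The cost is one covariate degree of freedom, a few sentences, and two simple rules: one for a missing baseline sample and one for below-detection values. No extra samples or assays are needed.

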### Outcomes

The effectiveness of the treatment will be measured based on severe OM being prevented and by the impact on the QoL of the participants. The levels of inflammatory cytokines in saliva will also be investigated.

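### QoL has no between-arm test, and the between-arm test of oral mucositis does not match the binary severe-OM endpoint that sized the trial

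*Protocol article*

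**What the plan says.** The Outcomes section sets two effectiveness measures: "The effectiveness of the treatment will be measured based on severe OM being prevented and by the impact on the QoL of the participants". The Participants section sizes the trial on the first of them, as a proportion: "we considered a prevalence of severe OM of 60% for the control group and 21% for the PBMT group". With 80% power and equal allocation this gives 50 participants, 25 per group. The Oral mucositis evaluation section defines severe OM as grade 3 or 4 on the NCI and/or WHO scale.

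The section Statistical analysis of data assigns tests by type of variable:

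- Pearson chi-square, between arms, for categorical clinical and demographic characteristics.
- Mann–Whitney, "used to compare the severity of OM and concentration of cytokines between the two groups".
- Friedman, within arms: "The Friedman test will be used to compare changes in outcomes in the different time points for each of the treatment groups".

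OHIP-14 and PROMS are named in none of these sentences. The Cost-effectiveness analysis section divides the cost difference by the between-arm difference in severe-OM frequency and, in two further ICERs, by the between-arm difference in QoL change from baseline to the 30th session. It states no test or interval for either difference. The only uncertainty analysis there is a univariate sensitivity analysis on parameters tied to the laser therapy.

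**The concern.** Two things do not line up.

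First, the Mann–Whitney sentence lists its outcomes and QoL is not among them. That leaves the Friedman test, done separately in each arm. It asks whether scores change over the visits in that arm. During radiotherapy they may well change in both arms for reasons unrelated to the laser, so the answer says nothing about the treatment effect. Yet the Discussion presents patient-reported outcomes as what is new in this trial, and two of the three ICERs divide by a QoL difference.

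Second, the power statement belongs to a comparison of two proportions, and no test of that comparison is named. The planned OM test ranks severity. It can be more or less powerful than the test used for sizing, depending on how the treatment moves patients among grades 0 to 2, which the sample-size calculation does not consider.

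At stake are a QoL result with no between-arm inference and an 80% power figure attached to a test that is not named.

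**Working it through.** **Step 1. Reproduce the sample size.** Inputs from the Participants section: p1 = 0.60, p2 = 0.21, alpha 0.05, power 80%, ratio 1:1. Two-sided testing is assumed, since sidedness is not stated. The mean proportion is 0.405 and the difference 0.39.

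- Pooled-variance formula: n = (1.960 + 0.842)² × 2 × 0.405 × 0.595 / 0.39² = 24.87, so 25 per arm and 50 in total.
- Fleiss formula without continuity correction: n = [1.960 × √(2 × 0.405 × 0.595) + 0.842 × √(0.60 × 0.40 + 0.21 × 0.79)]² / 0.39² = 23.66, so 24 per arm and 48 in total.
- Odds ratio: (0.21/0.79) / (0.60/0.40) = 0.177, which rounds to the stated 0.18.

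The stated 50 is reproduced exactly by the first formula. The trial was sized on a two-proportion comparison.

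**Step 2. Power of that comparison at 25 per arm.** Normal approximation: (0.39 × √25 − 1.960 × √(2 × 0.405 × 0.595)) / √(0.60 × 0.40 + 0.21 × 0.79) = (1.950 − 1.361) / 0.637 = 0.925, so power is 82%. Exact power of the uncorrected chi-square test is 85%, and of Fisher's exact test 76%.

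**Step 3. Power of the planned Mann–Whitney test with the same 60% vs 21%.** The grade distributions below are assumptions, because the protocol gives none. Power is by simulation with 25 per arm. The relative effect is the probability that a control participant has the worse grade, counting ties as half.

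| Scenario | Control, grades 0–4 | PBMT, grades 0–4 | Relative effect | Power |
|---|---|---|---|---|
| General shift | .05 .10 .25 .45 .15 | .15 .29 .35 .17 .04 | 0.6245 + 0.2065/2 = 0.73 | about 84% |
| Milder grades move the other way | .15 .20 .05 .45 .15 | 0 .09 .70 .17 .04 | 0.5040 + 0.1355/2 = 0.57 | about 19% |

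Both rows have 60% vs 21% in grades 3–4. The second is a deliberately unfavourable case.

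**Step 4. What within-arm Friedman tests can show.** Assumptions: 25 per arm, five visits, exchangeable correlation 0.5, and the same linear trend in both arms, so no treatment effect. The figures are the share of 1,500 simulated trials in which one arm is significant and the other is not.

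| Total trend (SD) | 0.2 | 0.4 | 0.5 | 0.8 | 1.0 | 1.5 |
|---|---|---|---|---|---|---|
| Discordant | 18% | 42% | 50% | about 21% | about 3% | 0% |

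The arms are independent, so with within-arm rejection probability p the discordance is 2p(1 − p). This peaks at 50% when p = 0.5 and falls again as p approaches 1. For steep trends both arms are significant, and that pattern does not show whether the treatment works either.

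**Step 5. Multiplicity, conditional.** The text does not say at which visit, or on which scale, OM severity is tested. If it were tested at all four post-baseline visits, each at 0.05, the chance of at least one false positive would be about 16%. If both scales were also tested (eight tests), it would be about 25%. These rest on assumed correlations of 0.3–0.6 between visits and 0.8 between scales. Independent tests would give 1 − 0.95⁴ = 18.5% and 1 − 0.95⁸ = 33.7%.

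**The case against.** A reader might infer that the planned analyses compare the arms on neither effectiveness measure. The protocol does not support that. The Mann–Whitney test compares OM severity between arms, and the cost-effectiveness section takes between-arm differences in severe-OM frequency and in QoL change.

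A reader might also infer that the QoL conclusion would rest on setting one arm's Friedman p-value against the other's. Nothing in the text says so. The Friedman figures show why such a contrast would be unsafe, not that it is planned. They also depend on trend size: with the pronounced decline that is plausible under radiotherapy, discordance nearly vanishes.

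On OM, severity could be read as the severe/non-severe split. On a binary variable Mann–Whitney is almost the chi-square test: for 15/25 vs 5/25 the p-values are 0.0043 and 0.0039. Even on graded severity, a general shift keeps power near 84%. The word clinical in the chi-square sentence might be stretched to include severe OM, although it describes participants' characteristics.

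Finally, an analysis plan that is not shown may add tests. Covariates, visit handling and missing data are properly left to it.

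What stands of this: the OM half is a mismatch to be reconciled, not a proven loss of power, and the multiplicity figures are hypothetical. What does not stand is treating the QoL gap as mere condensation. The section assigns tests outcome by outcome, and the only one that can reach QoL cannot answer the between-arm question.

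**Conclusion.** The concern holds in two parts.

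1. **QoL.** As written, the plan gives no between-arm inference on OHIP-14 or PROMS. The between-arm QoL difference exists only as an ICER denominator, without an interval. This follows from the text and needs no numerical assumption.
2. **Severe OM.** The 80% power applies to a comparison of proportions that no sentence names as a test. For the planned Mann–Whitney test on severity, power is not guaranteed: about 84% or about 19% under two assumed grade distributions with the same 60% vs 21%. The lower figure shows what is possible and is not a forecast.

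The conclusion goes no further. OM is compared between arms, and no contrast of within-arm p-values is planned.

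**What to change.** - **Severe OM (primary).** Compare the proportion with any grade 3–4 OM after baseline by chi-square, with risk difference and 95% CI. This matches the sample-size calculation and has about 82–85% power at 25 per arm (76% if Fisher's exact test were used instead). Keep Mann–Whitney on the worst grade as one secondary analysis, which also removes the question of repeated tests over visits.
- **QoL.** For each of OHIP-14 and PROMS, compare the arms with a baseline-adjusted model, either ANCOVA at the 30th session or a mixed model over visits. Report the between-arm difference with 95% CI. Relative to raw change, ANCOVA multiplies the variance by (1 − r²) / [2(1 − r)] = (1 + r)/2, a reduction of 40%, 25% or 10% if the baseline correlation r is 0.2, 0.5 or 0.8 (assumed values).
- **Friedman tests.** Label them descriptive.

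Cost: wording only. The variables are already collected, the named software can fit these models, and the sample size does not change. The change should be fixed before any outcome data are compared by arm.

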#### Oral mucositis evaluation

An assessor who is blinded to the treatment will conduct the OM evaluation. The researcher responsible for the PBMT will take intraoral pictures and save them on a hard disk for later evaluation. The evaluation will be in the first appointment and after the 7th, 14th, 21st and 30th RT sessions. The photographs will be taken using a T3i camera, with a circular flash (MR-14EX II) and a lens of Ef-s 18–55 mm F/3.5–5.6 (Canon, Tokyo, Japan). Pictures of the upper and lower labial mucosa, buccal mucosa, hard and soft palate, lateral surface of the tongue and floor of mouth will be acquired.

For the OM classification, the World Health Organization (WHO) [31] and the National Cancer Institute (NCI) [32] classifications will be used.

According to the WHO scale, the OM is classified as: 0, no signs or symptoms; 1, oral soreness and erythema; 2, erythema, ulcer, both solid and liquid diets tolerated; 3, ulcers and liquid diet only; 4, oral alimentation is impossible. The NCI scale is a graduated scale as follows: 0, no visible alterations; 1, presence of erythema; 2, noncontiguous ulcers up to 1.5 cm in diameter; 3, contiguous ulcers larger than 1.5 cm in diameter; 4, ulcers showing necrosis and bleeding. In this study, OM will be considered severe when classified with grades 3 or 4 according to the NCI and/or WHO scales.

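### The within-arm Friedman test drops a participant from an outcome's time-course analysis when one of five values is missing, and the plan makes such gaps foreseeable

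*Protocol article*

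**What the plan says.** The protocol article's section on statistical analysis of data states: "The Friedman test will be used to compare changes in outcomes in the different time points for each of the treatment groups". Between the arms it states: "The Mann–Whitney test will be used to compare the severity of OM and concentration of cytokines between the two groups". Mann–Whitney is thus named for OM severity and cytokines only. For OHIP-14, PROMS and nitrite, Friedman is the only test named.

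Each outcome has five measurements. For OM: "The evaluation will be in the first appointment and after the 7th, 14th, 21st and 30th RT sessions". For saliva: "The collection of saliva will be performed before initiating the HNC treatment and after the 7th, 14th, 21st and 30th RT sessions". The quality-of-life section gives the same five time points for both questionnaires.

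The Participants section sets a minimum of 25 per group, to which "an additional 10% was considered to compensate for possible loss to follow-up". It also sets a minimum radiotherapy dose of 50 Gy at 2 Gy per day. Participants who die, withdraw or miss five or more laser sessions are removed from the trial.

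**The concern.** The Friedman test compares ranks within a person across all time points, so it needs a complete block. If one of five values is missing for an outcome, that person's other four values for that outcome are not used either. With about 25 people per arm, a few scattered gaps shrink the analysed set noticeably.

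Two features of the plan make gaps foreseeable. The last assessment is tied to session 30, while the minimum course has fewer sessions than that. And the loss allowance counts whole participants, not missed visits or unusable samples.

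At stake is the power of the within-arm time-course results, most of all for the two questionnaires and nitrite, which have no other named test. The set analysed can also differ from outcome to outcome and between arms.

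**Working it through.** **The plan's own figure.** Severe OM 60% against 21%, two-sided 5% level, 80% power. With mean proportion (0.60 + 0.21)/2 = 0.405, the Kelsey formula gives n = (1.960 + 0.842)² × 2 × 0.405 × 0.595 / 0.39² = 24.87, so 25 per group and 50 in all. The stated minimum reproduces. The 10% is added on top, so 25 per arm is taken below as the number left after dropout.

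**Sessions.** 50 Gy / 2 Gy = 25 sessions at the minimum; session 30 corresponds to 30 × 2 = 60 Gy. Anyone receiving 25 to 29 sessions has no session-30 value, however well they attend. The article does not say how many that will be.

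**Complete blocks.** Let m be the probability that a value is missing at each of the four follow-up visits, independently, with baseline complete. The article gives no m; 2% to 10% is an assumed range. The share of complete records is (1 − m)⁴. The share of all five-visit data that is observed is 1 − 4m/5. The Friedman statistic is n(k − 1)W, with k = 5 and critical value 9.49, so the Kendall's W needed for significance is 9.49/(4n).

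| m | Complete share | Complete blocks of 25 | Data observed | W needed |
|---|---|---|---|---|
| 0 | 100% | 25 | 100% | 0.095 |
| 2% | 92% | 23.1 | 98% | 0.103 (n = 23) |
| 5% | 81% | 20.4 | 96% | 0.119 (n = 20) |
| 10% | 66% | 16.4 | 92% | 0.148 (n = 16) |

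**Power, illustrative.** The assumed outcome is continuous, with within-person correlation 0.5 and time means 0.6 × (0, 0.4, 0.8, 1, 1) SD. There are 25 per arm and values are missing at random positions. The ranges are over repeated simulations of 2,000 to 4,000 runs each. With complete data, power is about 71–73%.

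| m | Friedman, complete blocks | Skillings-Mack, all records |
|---|---|---|
| 2% | 68–69% | 71–72% |
| 5% | 61% | 70–72% |
| 10% | 48–51% | 67–69% |

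Type I error was about 5% for both tests. A second scenario (independent residuals, linear rise of 1 SD) gives the same picture for Friedman: 79% at 25 complete records, 75% at 23, 68% at 20 and 55% at 16.

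**OM grade.** The 0.6 SD rise does not represent this outcome. A simulation started everyone at grade 0 and took 60% of controls to grade 3 or 4. Friedman power was then about 100% with only 15 complete blocks. In the photobiomodulation (PBMT) arm, with 21% severe, it was about 99% at 15 blocks if half develop any OM, and fell to 51% only if nobody has mild OM.

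**The case against.** **The analysis plan is not shown.** It may hold a rule for gaps, including imputation, so complete-case analysis is the default of the named test and not something the article declares. That is fair, and the absence of such a rule is not the point here. The point is the choice of a test that needs complete blocks when alternatives using all the data exist.

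**Whole records are not lost.** A reader might infer that one missed sample deletes a person from the trial's analyses. It does not. A lost saliva sample affects the within-arm tests of the saliva outcomes only. The Mann–Whitney comparisons do not need five-visit records, and severe-OM incidence, which drives the sample size and the first cost-effectiveness ratio, does not use Friedman.

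**Dropout should not be counted twice.** Taking a further 10% from 25 gives 25 × 0.9 × 0.815 = 18.3 blocks at m = 5% and 25 × 0.9 × 0.656 = 14.8 at 10%. The Participants section adds the 10% on top of 25, so these figures overstate the loss. They would apply only if 50 were the total enrolled; the abstract gives 50 without mentioning the allowance.

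**The sickest.** It is tempting to infer that the worst-affected participants are the ones lost. The documents do not show this. Visits are numbered by RT session, so a suspension delays a visit and does not cancel it. Help is provided with the questionnaires. Those with short RT courses need not be sicker. The simulations assume missingness unrelated to outcome and so give no evidence of selection. Replacing Friedman would not undo the separate rule that removes participants after death, withdrawal or five missed laser sessions.

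**Significant in one arm, not in the other.** Unequal gaps could contribute to that pattern, but it can arise from separate within-arm tests even with complete data. It is a different issue.

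**Conclusion.** The point holds in a limited form. The named time-course test discards incomplete records outcome by outcome, in arms of about 25, and the 25-session minimum set against a session-30 visit makes some gaps structural.

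In the illustrative scenario, a rank test that keeps incomplete records recovers about 3 power points at 2% missing per visit, 9 to 11 at 5%, and 16 to 19 at 10%. These figures rest on an assumed missing rate, independent gaps, 25 per arm after dropout and an assumed effect. The article gives no effect size for cytokines, nitrite or quality of life. The gain was computed for Skillings-Mack, not for a mixed model. The structural gap at session 30 is not included and would add to the loss by an unknown amount.

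The loss is minor if few values are missing, and no material loss is shown for OM grade, where the expected change is large. The sample-size endpoint is untouched. Biased trajectories through loss of the sickest remain a possibility, not a finding. The change is still worth making, because it uses data already collected.

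**What to change.** In the section on statistical analysis of data, replace the Friedman test with one repeated-measures model per outcome that uses all available visits, with terms for arm, visit and arm-by-visit:

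- a linear mixed model for log cytokines, nitrite, OHIP-14 and PROMS;
- an ordinal mixed model or ordinal GEE for OM grade.

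If a rank test is preferred, use the Skillings-Mack test, which equals Friedman when data are complete. In either case, report the number contributing at each visit by arm for each outcome, including how many reach session 30.

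The cost is a change of wording and modest extra analysis; no new data are needed. The downside is added assumptions. The mixed models need distributional assumptions and data missing at random; GEE needs data missing completely at random. Skillings-Mack avoids the distributional assumption but still takes missingness to be unrelated to outcome, so it restores power without curing any selective loss.
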